### Procedure and recruitment

#### Patients

Cancer patients will be recruited via the respective visceral oncology centers of the three study sites. The eligibility criteria will be assessed by the study coordinators. If patients decline to participate in the study, a 3–5 min interview will be conducted to capture reasons for refusal, previous screening and psycho-oncology experiences, and information about the current disease. The participants receive the same questions in the questionnaire. If the inclusion criteria are fulfilled and the patient is interested in participating in the study, a detailed explanation is given in a personal interview (informed consent) after the initial contact with the patient. If the person declares their willingness to participate, a signed consent form is obtained.

In addition to the screening, the patients receive a questionnaire package (approximately 30–40 min) at t0 and t1 (Table 1). Furthermore, demographic, medical and treatment-related data are collected. The patients receive the questionnaires in person (at t0 during the inpatient stay) and by mail or e-mail as an online survey via link (at t1). The online questionnaire will be provided via a secure online survey platform (UniPark). Completed questionnaires will be collected by the study nurse and the study coordinators. If questionnaires are not received at t1, a reminder will be sent (by mail or e-mail) after 2 weeks.

**Table 1 Tab1:** Measurement instruments

Questionnaire	CG t0	CG t1	IG t0	IG t1
*Basic data*				
Demographic, medical and treatment-related data	x	x	x	x
*Screening*				
Distress (NCCN-DT)	x	x	x	x
Corona-DT	x	x	x	x
Knowledge about psycho-oncology (OptiScreen Questionnaire)	x	x	x	x
*Psychological functioning*				
Depression (PHQ-9)	x	x	x	x
Anxiety (GAD-7)	x	x	x	x
Quality of life (SF-8)	x	x	x	x
Fear of cancer recurrence (PA-F-KF)	x	x	x	x
Health literacy (HLS-EU-Q16)	x	x	x	x
Support needs (SCNS-SF34-G)	x	x	x	x
Social support (ISSS)/SSUK-8)	x	x	x	x
Body image (BIS)	x	x	x	x
Patient activation (PAM-13D)	x	x	x	x
Satisfaction with care (REPERES-33-G)	x	x	x	x
Relationship satisfaction (OMI-D)^a^	x	x	x	x
Sexuality (SBQ-G)	-	-	x	x

*Notes* CG = comparison group; IG = intervention group; NCCN-DT = National Comprehensive Cancer Network Distress Thermometer (Mehnert et al. 2006a, b); Corona-DT = Adapted version of the DT to measure psychological distress from the Covid-19 pandemic, PHQ-9 = Depression module of the Patient Health Questionnaire (Kroenke et al. 2001); GAD-7 = Generalized Anxiety Disorder Questionnaire (Spitzer et al. 2006); SF-8 = Short Form-8 Health Survey (Ware et al. 2001); PA-F-KF = Fear of progression Questionnaire, short version (Mehnert et al. 2006a, b); HLS-EU-Q16 = European Health Literacy Questionnaire (Sorensen et al. 2013); SCNS-SF34-G = Supportive Care Needs Survey, short form (Sklenarova et al. 2015); ISSS/SSUK-8 = The Illness-specific Social Support Scale (Ullrich and Mehnert 2010); BIS = Body Image Scale (Hopwood et al. 2001); PAM-13D = Patient Activation Measure (Brenk-Franz et al. 2013); REPERES-33-G = Recherche Evaluative sur la Performance des Réseaux de Santé, German short version (Defossez et al. 2007); QMI-D = Quality of Marriage Index (Zimmermann et al. 2015); SBQ-G = Sexual Behavior Questionnaire (Müller and Gensch 2003)

^a^only for patients in relationships

All patients are given a code to ensure anonymity. All study documents will be stored in locked cabinets, and data will be stored in password-protected files accessible only to the study team.

The comparison sample (CG) is collected at baseline as a care-as-usual condition. The survey will take place before the OptiScreen-Training is conducted.

To survey the intervention group (IG), after conducting the oncology nursing training, the trained nurses are assigned per site to conduct the screening. Their task is to screen all inpatients for psychosocial distress using the screening instrument, e.g., the Distress Thermometer (Mehnert et al. 2006a, b). The nurses evaluate the screening and also consider the clinical impression of the treatment team. When performing the screening, the nurses take into account the aspects taught in the training regarding framework conditions and obstacles. In case of elevated distress, further psycho-oncological diagnosis and care is provided by the psycho-oncology team, which in turn provides feedback on the patient's psychological distress to the medical treatment team in a feedback loop. If there is no to low stress, a low-threshold information offer (e.g., flyer) is made.

#### Psycho-oncology team

To obtain a validated external assessment of patients' psychological distress and support needs, information will be collected by the psycho-oncology team after the initial consultation with patients (assessment sheet psycho-oncological consultation). In addition, the psycho-oncology team will be surveyed after the OptiScreen-Training has been conducted to assess acceptance, satisfaction, and changes in nurses' attitudes and behaviors regarding the psycho-oncology screening process.

#### Nurses

Nursing staff will also be surveyed on satisfaction, feasibility and acceptance of the OptiScreen-Training via questionnaire (paper–pencil). The pre-questionnaire for the nurses is completed two weeks prior to the training, the post-questionnaire immediately after the OptiScreen-Training. Nurses choose a personal code for anonymity to compare the pre- and post-questionnaires.

#### The “OptiScreen-Training”

The concept of the OptiScreen-Training is based on qualitative analyses of nurses training needs (Dreismann et al. 2022) as well as literature, evidence-based examples, and a workshop with experienced psycho-oncologists. To achieve a good fit of the training and the needs of nurses, we conducted interviews with 15 experts on nursing from all three study locations to determine barriers, requirements and major questions (Dreismann et al. 2021, 2022). The OptiScreen-Training consists of three main thematic modules (Fig. 3) that can be taught in one day or on three different dates, each lasting about 2 h as face-to-face sessions. Module 1 focuses on psycho-oncological care and possible mental disorders in cancer patients. Module 2 addresses psychological distress and the screening process. Module 3 aims to train communication during the screening process and teaches basic approaches to self-care. All modules include theoretical knowledge transfer as well as practical exercises such as role plays, group-work, case discussions and take place in groups of 4–15 nurses. All trainings are conducted by trained psychologists with expertise in psycho-oncology and are recorded to ensure comparability. The trainings are conducted on-site at the three study sites. To maintain the learning effect of the training, concepts such as booster methods (e.g., booster session 1 year after the initial training) and refresher techniques (e.g., postcards) are developed to remind nurses to integrate the screening into their daily work.

**Fig. 3 Fig3:**
[figure not shown]
Modules of the OptiScreen-Training

For the successful implementation of the screening process after training, a local study nurse supports the nursing staff at all three sites in the implementation and evaluation of the screening as well as the referral to psycho-oncology. With the help of the study nurse, the nurses try to overcome barriers and obstacles of the patients regarding the screening through advisory exchange with each other. The study nurse is in direct exchange with the psycho-oncology team. She is also a multiplier for the optimized screening in the medical team (e.g. nurses, casemanagement, physicians) and answers questions regarding the process or specific cases. The study nurse tries to reduce barriers and obstacles in communication and utilization of the screening and to optimize the implementation in the daily clinical routine.

#### Measurement

To measure the study objectives the following outcomes should be captured: (a) psychological distress of patients, (b) utilization of psycho-oncological support, (c) information about psycho-oncological services, (d) treatment satisfaction, (e) acceptance and practicability of OptiScreen-Training by caregivers, (f) assessment of access to and utilization of support services, barriers and facilitating factors for utilization of psycho-oncological services. A list of measurement instruments is presented in Table 1.

#### Primary outcomes

Mental distress of patients (identified as mentally distressed by optimized screening, receive a psycho-oncology consultation and further diagnosis by psycho-oncology verifies mental distress) is the primary outcome. To assess distress, the German version of the National Comprehensive Cancer Network Distress Thermometer will be used (Mehnert et al. 2006a, b). General distress is measured on a visual analogue scale ranging from 0 = no distress to 10 = extreme distress. A score of 5 is internationally recommended as an indicator that a patient is distressed and needs support (National Comprehensive Cancer Network 2020). Further 36 potential causes of distress that are grouped in five subscales, i.e., (1) practical problems, (2) family problems, (3) emotional problems, (4) spiritual/religious concerns, (5) physical problems and an open answer option for possible other problems are assessed using the problem checklist (yes/no).

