## Identification of psychosocial distress

Brief distress screening questionnaires should thus increase referral to psychosocial interventions (Andersen et al. 2014; Fitch et al. 2018). In accordance with the S3 guideline Psycho-oncology (Weis et al. 2022; Leitlinienprogramm Onkologie 2014), the following screening methods are recommended: Distress Thermometer (DT) (Mehnert et al. 2006a, b), Cancer Patient Stress Questionnaire (Book et al. 2011), Hospital Anxiety and Depression Scale (Herrmann-Lingen et al. 2011), and Patient Health Questionnaire (Kroenke et al. 2001) as well as Generalized Anxiety Disorder Scale-7 (Spitzer et al. 2006). However, the use of a screening procedure does not ensure that all persons screened as burdened are identified and also referred to psycho-oncological care. Often, patients are referred to psycho-oncology through their own initiative or through the initiative of a member of the medical team. This can lead to a not inconsiderable number of patients who need support not receiving it, because they may be too burdened to request it or, without a standardized approach, have difficulty finding appropriate help (Carlson et al. 2010). Furthermore, the use of screening does not seem to automatically lead to distressed patients also seeking psycho-oncological support (Funk et al. 2016). Only about 20–40% of highly distressed cancer patients make use of psychosocial services (Dilworth et al. 2014). In certified oncology centers, the utilization rate was 11% (Singer et al. 2013). Reasons for this are that patients often deny psychosocial problems and are afraid of stigmatization, "want to make it on their own" or "have to be strong", "do not want to be a burden to others—including the treatment team" or possibly do not understand the term "psycho-oncological support". In addition, there is a lack of information about the available services and unclear ideas about their benefits (Weis and Giesler 2016). In a multicenter, cross-sectional study in Germany by Faller et al. (2016) with 4020 cancer patients with different tumor entities only 38% of patients reported feeling sufficiently informed about psycho-oncological care. Furthermore, 36% requested more information about psycho-oncological support services. Moreover, insufficient communication between patients, physicians and nurses can be the cause. Thus, the implementation of a screening often has no influence on the use of psycho-oncology support (Braeken et al. 2013). Challenges of screening include overestimation or underestimation of mental distress as well as acceptance of the screening instrument. Furthermore, the mere use of a screening instrument cannot reliably measure emotional distress (Mitchell et al. 2011). However, if the screening (DT) is combined with a personal conversation and referral offers, the use of psycho-oncology support also increases (Carlson et al. 2010). In addition, the confidence as well as the skills of the clinician also have a positive impact on successful screening (Mitchell et al. 2011).

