## The present study

Based on these preliminary findings, the primary objective of the study was derived: to optimize and professionalize the psychosocial screening process by training oncology nurses and developing an interdisciplinary care algorithm, thereby improving the targeted identification of mental distressed patients and the referral to psycho-oncology care as needed.

The postulated model of this study (Fig. 1) for the precise identification of distressed patients and for the provision of needs-oriented psycho-oncological care takes various processes into account. From all cancer patients, the mentally distressed patients have to be identified with the help of a screening. In the next step, these mentally distressed patients must also be provided with psycho-oncological care in line with their needs. The last step is to check whether the patients identified by the screening need psychosocial support through further psycho-oncological diagnostics—also for the diagnosis of mental disorders. In addition, barriers and obstacles need to be identified.

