#### Secondary outcomes

Information about psycho-oncology services, treatment satisfaction, patient competence and quality of life are secondary outcomes as well as acceptance and practicability of the OptiScreen-Training, assessment of access to and utilization of support services, barriers and facilitating factors for the utilization of psycho-oncological services.

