#### Statistical measures

First, the primary and secondary outcomes as well as all patient characteristics are analyzed descriptively together and separately for the two groups (means, standard deviations, frequencies). The primary outcome, psychological distress, is analyzed by ANCOVA (analysis of covariance) including variables such as tumor stage, age, and gender as covariates. This usually even increases the power of an ordinary *t* test. Missing values are replaced using multiple imputation. In sensitivity analyses, the results of the primary analysis are checked for consistency. Differences in secondary outcomes are evaluated between intervention and comparison groups or between appropriate subgroups analogous to the primary analysis using univariate or multivariate procedures or appropriate regression models. Depending on the distribution of the target parameter, binary or ordinal logistic mixed model regressions and linear mixed model regressions will be used. Before starting the analysis, the exact procedures are defined in a statistical analysis plan. Moderator as well as mediator analyses are used to identify barriers to take-up, as they can test complex relationships between several variables in the form of a priori models. The evaluation of the training will be analyzed using *t* tests (pre and post).

To control for possible selection effects that could lead to sampling bias, reasons for non-participation and sociodemographic and medical data of the non-participants will be analyzed. In this way, possible selection effects can be identified and the interpretation of results may be adjusted as necessary. Possible confounding variables are analyzed in inferential statistical analyses (e.g., regressions) using important covariates (age, gender, tumor entity, stage) as well as other theory-based influencing factors, e.g., physical comorbidities controlled.

Missing values due to drop-outs are replaced and can be predicted by means of multiple imputation, in that for the missing values, estimated values are used, which are calculated by distributing different predictors. This is done by taking all available relevant information of the data set into account and including random errors. The advantage is a low loss of information, since all variables remain included in the model. In addition, standard errors, which are moreover caused by the multiple repetition of the estimation process are randomly and realistically calculated and included.

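### The primary outcome is worded as a three-step care pathway but measured, powered and analysed as a distress score; these are two different endpoints and nothing in the protocol reconciles them

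*Protocol article*

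**What the plan says.** All references are to the protocol article.

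- **The present study** gives the primary objective as optimizing the screening process, "thereby improving the targeted identification of mental distressed patients and the referral to psycho-oncology care as needed". Objective 2 under **Study objectives** follows the same steps: screening cut-off, consultation, further diagnostics.
- **Primary outcomes** names mental distress of patients and adds in brackets: "identified as mentally distressed by optimized screening, receive a psycho-oncology consultation and further diagnosis by psycho-oncology verifies mental distress". It then turns to the Distress Thermometer: "General distress is measured on a visual analogue scale ranging from 0 = no distress to 10 = extreme distress". A cut-off is mentioned ("A score of 5 is internationally recommended as an indicator that a patient is distressed and needs support"), but no analysis is tied to it.
- **Sample size and power calculation** powers mental distress, intervention group (IG) against CG, on an effect size of 0.3 with 80% power and 190 evaluable patients per group. No event rates are given.
- **Statistical measures** states: "The primary outcome, psychological distress, is analyzed by ANCOVA (analysis of covariance) including variables such as tumor stage, age, and gender as covariates". The ANCOVA is compared with an ordinary t test. Binary logistic models are mentioned only in connection with the secondary outcomes.
- **Secondary outcomes** includes "assessment of access to and utilization of support services", and **Measurement** lists distress and utilization as separate items.

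**The concern.** The bracket describes something that happens to a patient: screened positive, seen by psycho-oncology, distress confirmed. It is true or false for each patient. The Distress Thermometer score is a number from 0 to 10 that records neither a consultation nor a clinical confirmation. The power statement and the analysis fit the score, whereas the primary objective fits the pathway.

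What is at stake is whether the primary test answers the primary question. None of the seven numbered objectives, nor the training aims (a) to (e), is to lower the average distress score. If the ANCOVA is run as planned, a training that gets many more distressed patients identified and referred could still produce a null primary result. A shift in the score could equally be reported as success with no change in referral.

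**Working it through.** **1. The plan's own sample size.** Inputs: effect size 0.3 and power 80% (Sample size and power calculation). Alpha is not stated; I assume 0.05 two-sided. For a comparison of means,

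n per group = 2 × (1.960 + 0.842)² / 0.3² = 174.4, so 175 (176 by the exact t test).

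The stated 190 is not reproduced. It gives about 83% power, so it is mildly conservative for a difference of 0.3 SD. If 0.3 were instead an effect size for proportions (Cohen's h), n would be about 175 to 183 for control rates from 5% to 40%. The sample size alone therefore does not reveal which endpoint was powered. The ANCOVA and the t-test comparison do: they point to a continuous score.

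**2. The two versions side by side.**

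| | Pathway (bracket) | Distress Thermometer score |
|---|---|---|
| Type | yes/no per patient | 0 to 10 |
| Matches the primary objective | yes | no |
| Matches the power statement and ANCOVA | no | yes |
| Defined in the CG as worded | no, because CG identification is care as usual | yes, Table 1 lists it for both groups at t0 and t1 |
| Success, inferred from the aims | more completions | lower score |

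**3. Could the bracket define the patients whose score is analysed?** This would select patients on events that follow the intervention, so the CG and IG subsets would not be comparable. It also fails on numbers. Inputs: 300 CG patients; half to two-thirds significantly distressed (Introduction); and "Only about 20–40% of highly distressed cancer patients make use of psychosocial services" (Identification of psychosocial distress).

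- Low: 300 × 0.50 × 0.20 = 30
- High: 300 × 0.667 × 0.40 = 80
- At the 11% utilization quoted for certified centers: 300 × 0.11 = 33

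These counts precede verification and any dropout, and 190 evaluable are required. The product is approximate, because the first rate refers to significant distress and the second to highly distressed patients. The conclusion does not depend on it. At two-thirds distressed there are 200 such CG patients, and 190/200 = 95% would have to complete every step and be evaluable. At one half there are only 150.

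**4. Power if the pathway were primary.** The article states no pathway rate, so these are assumed scenarios: 300 CG, 600 IG, no loss, alpha 0.05 two-sided. With pooled rate p̄ = (300p₁ + 600p₂)/900,

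se₀ = √[p̄(1−p̄)(1/300 + 1/600)], se₁ = √[p₁(1−p₁)/300 + p₂(1−p₂)/600], power = Φ[(p₂ − p₁ − 1.96 se₀)/se₁].

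For 11% against 18%: p̄ = 0.157, se₀ = 0.0257, se₁ = 0.0239, and power = Φ[(0.07 − 0.0504)/0.0239] = Φ(0.82) = 79%.

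| CG | IG | Power |
|---|---|---|
| 11% | 21% | 97% |
| 11% | 18% | 79% |
| 11% | 16% | 52% |
| 7% | 12% | 65% |
| 5.5% | 9% | 45% |

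The 11% is utilization. The pathway also requires a positive screen and confirmed distress, so its rate cannot exceed utilization and would probably be lower.

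**The case against.** The best defence is that the head noun is distress throughout. Sample size, Measurement and Statistical measures all name distress, the Distress Thermometer follows directly after the bracket, and utilization is listed separately. On that view the bracket only describes which patients are meant. It is fair that the text does not say outright that the primary outcome is a binary composite. But the subset reading fails on step 3, and deleting the bracket would leave a primary analysis that does not test the primary objective.

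A second defence is that exact procedures are deferred to a statistical analysis plan, which is not shown. This rules out two inferences a reader might draw: that the endpoint will be chosen after seeing the data, and that a time point missing from the article is in itself an error. It does not remove the conflict, because the article itself fixes the outcome wording, the power basis and the method.

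Other stronger readings are also unsupported:

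- **Opposite directions as a stated fact.** No direction is written for the primary test. It follows only from the aims of increasing referral and reducing distress.
- **Only additionally referred patients can benefit, so the effect on the mean is diluted by a calculable factor.** Patients with little or no distress are offered information, and a study nurse supports the whole process. Any such factor would also need an assumed rise in uptake.
- **Half the t1 data will be missing.** The 50% is applied both to recruited patients and to the case pool before recruitment. Moreover, 190/270 = 70% retained, which implies about 30% loss. The figure cannot carry that claim.
- **Utilization as a secondary outcome is an error.** It overlaps with one pathway step, but components are normally reported separately.

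**Conclusion.** The point holds as an unreconciled primary outcome. The pathway in the bracket and the distress score in the power and analysis sections are different endpoints. The pathway as worded has no value in the CG, and no reading of the bracket makes the sections agree. This rests on the text and needs no assumed rates. The 30 to 80 CG patients in the subset check depend on the background rates the article quotes, but the shortfall against 190 is large enough to survive their imprecision.

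That success on one endpoint could accompany a null result on the other is a consequence of their being different. That they point in opposite directions is an inference from the aims. The power figures for the pathway are illustrations only. This should be settled before any outcome data are analysed.

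**What to change.** State one primary outcome, defined identically in CG and IG, with its time point, direction, matching model and power statement. Two routes are open:

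- **(a) Distress score.** Delete the bracket. Name the Distress Thermometer score at t1 as primary, lower being better, analysed by ANCOVA adjusted for the t0 score. Report identification and referral as a key secondary outcome.
- **(b) Pathway.** Make the pathway primary. Replace the reference to optimized screening with one study Distress Thermometer rule, and use the same consultation sheet in both groups. Analyse by logistic regression with a risk difference and confidence interval. Restate the power over a range of assumed rates, including rates below 11%.

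Under either route, keep utilization as a separately reported secondary outcome.

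**Cost.** Protocol wording and a revised power statement; one of the two claims becomes secondary. Route (b) carries more. The sponsor must confirm that the consultation sheet is completed in the CG, since it is not in Table 1 and its use there is not stated. Verification would be made by psycho-oncologists who know the training has taken place. A rule based only on the score would leave out referrals prompted by the team's clinical impression. The pathway rate would also rise if distress itself became more common between the two periods, which a before-after design cannot separate from the training.
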